#### Clinical Outcomes

In addition to patient satisfaction, anxiety before and during surgery will be assessed. Comparison of patient satisfaction and anxiety measures between the intervention and control groups will be conducted. Additionally, patients in the intervention group will be asked at the end of the operation day whether they would choose to use the goggles again during potential follow-up surgery. For these patients, the average STAI score will be compared between those who would opt to use the goggles again and those who would not. Furthermore, comparisons of the recorded vital parameters and scores at different time points during surgery will be made between the control and intervention groups.

### Data Collection and Management

Missing data are not expected; however, if data are incomplete for a participant, the participant will be excluded from the analysis. Group allocation and reasons for exclusion will be reported transparently to minimize the risk of bias. Due to the pilot nature of the study, no imputation is planned.

Patient-specific data and collected parameters are recorded on paper case report forms and later manually entered into a Microsoft Excel database. The complete dataset will be transferred to an SPSS (version 28, IBM Corporation) database for analysis. Digital data are stored in a folder with restricted access on a protected server of the University Hospital Augsburg. Paper-based data are stored in a locked office at the study office. Final data access is only granted to primary investigators.

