### Randomization

Patient randomization follows a predefined list based on patient ID, assigning them to either the control or intervention group. The list is followed sequentially, and random assignment to either the intervention or control group is performed using Microsoft Excel. The randomization scheme is constructed to ensure a 1:1 allocation ratio (50-50) upon reaching a total sample size of 100 patients. Due to the nature of the intervention, blinding of participants and investigators is not feasible.

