### Sample Size Estimation

Due to the exploratory nature of the study, no formal sample size estimation was performed. There are no other studies covering this topic. Therefore, there are no data available on how great a relevant effect should be, nor on how large the sample size should be. The goal is to use this study and its preliminary results as a basis for initiating a confirmatory trial. With a sample size of 100 patients, the sample should be big enough to provide an overview on the possible characteristic values.

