### Assessment of Distress

To assess patient stress, questionnaires and vital/laboratory parameters will be used. The day before surgery, after they provide informed consent, the patients will complete initial questionnaires. These include the Spielberger State-Trait Anxiety Inventory (STAI; Hogrefe Verlag), which measures both “trait anxiety” (a general predisposition to anxiety) and “state anxiety” (anxiety related to the current situation, ie, the upcoming surgery) [11]. This questionnaire is often used to measure anxiety and is seen as an indicator of distress. The score is used in many types of analysis, although the trait sections of the STAI are believed to measure negative affectivity rather than trait anxiety per se [12,13]. Additionally, patients will complete the Kurzfragebogen zur aktuellen Beanspruchung (KAB; German for “short questionnaire for acute stress”), which will be repeated perioperatively multiple times to assess changes in response patterns [14]. The focus will be on individual stress trajectories and differences between the control and intervention groups.

For a more objective measurement of stress, the cortisol level in the serum is measured by taking blood samples at multiple times (at baseline, arrival in the operation room, skin incision, clamping the carotid artery, skin suture, and 1 hour after skin suture). Baseline measurements are all taken under consistent conditions: the same time of day before the patient rises from bed. Resting heart rate, KAB score, and the Richmond Agitation-Sedation Scale (RASS) score will be evaluated simultaneously with blood sampling. Cortisol levels are a common tool to measure stress in acute situations [15-17]. The RASS, commonly used in anesthesiology and intensive care, will be used to estimate patients’ agitation and provide insight into their stress levels [18]. Heart rate and RASS scores serve as objective measures of patient stress, while the KAB reflects patients’ subjective burden across 6 categories. This score is frequently used in psychology to capture current stress levels and is well suited for perioperative use due to its ease of administration. The differences in serum cortisol levels between the groups are considered the primary end point. All other measurements are secondary end points.

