### Outcomes

#### Primary Feasibility Outcomes

Patients who meet the inclusion criteria and agree to participate are enrolled in the study. Patients who meet the criteria but decline participation are counted anonymously, with differentiation between those who refuse and those who are excluded for other reasons (eg, language barriers, profound hearing impairment, dementia, or logistical challenges). After the operation is completed and the patient leaves the wake-up room, all data are checked for completeness, and an attempt is made to fill in any missing data. If there any adverse events or remaining missing data, or if the patient withdraws consent to participate in the study, the collected data are excluded from analysis. Because of the very short time from patient inclusion to complete data collection for each patient and because there is no follow-up after the initial inpatient stay, we assume that this method will yield mostly complete records.

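### Any remaining gap removes the whole participant from every analysis, so an unrelated missing item discards valid primary-endpoint cortisol values and can select who stays in the comparison

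*Protocol article*

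**What the plan says.** The rule appears twice in the Methods. Under Data Collection and Management: "if data are incomplete for a participant, the participant will be excluded from the analysis". Under Primary Feasibility Outcomes, the listed grounds for exclusion continue: "or remaining missing data, or if the patient withdraws consent to participate in the study, the collected data are excluded from analysis". Neither statement confines the exclusion to the endpoint with the gap.

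Three statements surround the rule:
- A retrieval step comes first. Once the patient has left the wake-up room, "all data are checked for completeness, and an attempt is made to fill in any missing data".
- The expectation is optimistic: "Missing data are not expected". Primary Feasibility Outcomes is more cautious and assumes only that most records will be complete, because the observation period is short and there is no follow-up after the inpatient stay.
- "Due to the pilot nature of the study, no imputation is planned". Allocation and the reasons for exclusion are to be reported.

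Assessment of Distress names serum cortisol, sampled at six times, as the primary endpoint. At those times "Resting heart rate, KAB score, and the Richmond Agitation-Sedation Scale (RASS) score will be evaluated simultaneously with blood sampling". The other measures are secondary. Planned Analysis is descriptive.

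**The concern.** The primary endpoint uses six values per patient. The rule makes their use depend on some thirty others, including ratings by the surgeon and the anesthesiologist. A patient with all six cortisol results and one missing RASS at clamping drops out of the cortisol comparison.

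Two things are at stake. The first is needless loss of data in a trial fixed at 100 patients, for which "no formal sample size estimation was performed". The second is selection after randomisation. Gaps at incision, clamping and suture are plausibly more frequent in distressed patients or difficult phases of surgery, and distress is what the goggles are meant to change. The article does not document this mechanism, but the rule gives it a route into every comparison.

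The rule also works against the trial's own aim of finding out which parameters can measure a benefit. That requires each parameter to be judged on its own data.

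**Working it through.** The article states no missingness rate, expected loss or item count, so there is no figure to reproduce.

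**Items per patient** (Abstract; Assessment of Distress; Assessment of Usefulness and Practicality)
- Cortisol, heart rate, KAB and RASS at six times: 4 × 6 = 24
- State-Trait Anxiety Inventory, state and trait: 2
- Surgeon and anesthesiologist, three ratings each: 2 × 3 = 6
- Patient ratings (satisfaction, anxiety before, anxiety during): 3
- Nausea or vomiting: 1

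The sum is 24 + 2 + 6 + 3 + 1 = 36. Depending on how the day-before KAB, the patient ratings and the goggle-only items are counted, the range is about 35 to 39. Each KAB counts as one item although it covers six categories.

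**Loss under the rule.** Let p be the assumed share of items still missing after retrieval. With independent gaps over k items, the share of patients deleted is 1 − (1 − p)^k.

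| p (assumed) | k = 36, all items | k = 18, cortisol, KAB and RASS only | k = 6, cortisol only |
|---|---|---|---|
| 0.1% | 3.5% | 1.8% | 0.6% |
| 0.5% | 16.5% | 8.6% | 3.0% |
| 1% | 30.4% | 16.5% | 5.9% |
| 2% | 51.7% | 30.5% | 11.4% |

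The middle column (3 measures × 6 times = 18) assumes that retrieval recovers everything else: postoperative ratings can still be requested, and heart rate may be on the anesthesia record (an assumption). The last column is the loss if deletion is confined to patients lacking one of the six cortisol values. A comparison at a single time point would lose only p itself.

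**Clustering.** If gaps concentrate in certain patients, fewer patients are affected at the same p. A simulation with equally correlated (probit) missingness at p = 1% gives:

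| Correlation | 36 items | 6 cortisol values |
|---|---|---|
| 0 | 30.4% | 5.9% |
| 0.2 | 23.7% | 5.5% |
| 0.5 | 14.6% | 4.6% |
| 0.8 | 6.7% | 3.1% |

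**Precision, for illustration.** The approximate 95% half-width for a difference in means, in SD units, is 1.96 × √(4/N). N = 100 gives 0.39 and N = 70 gives 0.47. The plan sets no precision target, so this breaches nothing stated.

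**Imbalance from item counts.** Allocation is "1:1 allocation ratio (50-50) upon reaching a total sample size of 100 patients". At p = 1%, 50 × 0.99^36 = 34.8 patients remain in an arm with 36 items. With one more item, 50 × 0.99^37 = 34.5 remain.

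**The case against.** The strongest reply is that this is a descriptive pilot with short observation, a completeness check before exclusion and a commitment to report exclusions by arm. On that view losses will be small and visible, and no power claim depends on them.

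Much of this stands. Many of the 36 items are postoperative and can simply be asked for again, so the 36-item column may overstate the loss. If gaps gather in agitated patients, as the selection argument supposes, independence overstates it further. Reporting exclusions makes the selection visible.

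Three parts do not stand. Retrieval cannot produce a blood sample that was not drawn, or a genuine KAB or RASS from the moment of clamping. The absence of follow-up guards against dropout, not against missed moments in the operating room. Disclosing a selected comparison does not restore the randomised one.

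A reader might infer more than the article supports:
- **That up to a third of the trial will be lost.** This is neither a figure in the article nor a bound. With 36 independent items it needs p of about 1.12%; the loss is smaller at lower rates or with clustering, and exceeds half at 2%.
- **That the extra goggle-arm question unbalances the arms.** The effect is 34.8 against 34.5 patients retained.
- **That recalled values will be entered as if taken on time.** The article names no source for filling gaps. It leaves this possible in an unblinded trial but does not describe it as practice.

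**Conclusion.** The concern holds for the rule itself. Exclusion is by participant rather than by endpoint, it is stated explicitly in two places, and it discards valid cortisol data because of gaps elsewhere. It is a stated choice, not a detail left to an analysis plan.

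The size is conditional. If 0.5% to 1% of items stay missing independently, about 17% to 30% of patients are lost when all 36 items count, or about 9% to 17% when only the 18 time-locked values are unrecoverable. Limiting deletion to cortisol costs 3% to 6%. Within-patient clustering lowers the loss and narrows the gap between the rules. The rates are assumptions, and so is the split between recoverable and unrecoverable items.

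Selection is a plausible risk whose direction and size the article does not allow anyone to estimate. It rests on gaps being related to distress or to conditions during surgery, not on a difference in item counts between arms.

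**What to change.** 1. Replace participant-level exclusion, in both sections, with analysis of each outcome on all its available values. For cortisol, a mixed model over the time points is an option that keeps patients with some samples missing and needs no imputation. A descriptive pilot does not require it; available-value summaries by time point are enough.
2. Limit later completion of time-locked measures to contemporaneous records, such as the anesthesia record or the laboratory system. KAB and RASS not taken on time stay missing.
3. Report missingness by arm and time point, alongside the exclusion reasons already promised.

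The cost is a change of wording, with no new data and no imputation. The drawback is that the number analysed will differ between outcomes, so each table must show its own denominators. About 90% of recruitment was complete at the article's final submission and analysis is due after the 100th patient, so the change should be made and dated before the data are analysed.

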### Planned Analysis

The analysis will be conducted using SPSS. Due to the study’s exploratory nature, descriptive statistics will be applied. Appropriate measures of central tendency and variability will be used depending on the level of measurement. Graphical representations will be made using line graphs or box plots.

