**Objective:**

We aimed to (1) determine whether there is a benefit for patients regarding stress reduction when using video goggles during vascular surgery of the carotid artery and (2) determine whether any parameters can effectively measure such a potential benefit.

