### Strengths, Limitations, and Dissemination

To evaluate patient stress, we use a multimodal approach that includes objective and subjective parameters. Serum cortisol levels serve as the primary objective marker, complemented by heart rate monitoring and the RASS. Additionally, the KAB questionnaire was used to assess patient-perceived stress. All parameters were recorded at multiple time points before, during, and after the operation, enabling a comparative analysis comparing the intervention and control groups.

Drug administration was meticulously documented, as medications could potentially confound the measured parameters. Although the sample size is limited, which may preclude statistically significant findings, and this is a single-center study, which means that just one device in one specific procedure is evaluated, the study primarily aims to assess the feasibility and acceptance of video goggles by patients, anesthesiologists, and surgeons, as well as to identify robust parameters for future research. By publishing our findings in a peer-reviewed journal, we hope to provide a basis for further research in this field and to promote enhanced approaches to perioperative stress reduction in patients undergoing carotid surgery under local anesthesia. In future work, a potential third group using music as a distraction tool could be explored.

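### The primary cortisol end point names no time point or summary, and the descriptive-only analysis gives no between-group estimate with uncertainty to match the first objective

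*Protocol article*

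**What the plan says.** **Objective (Abstract).** The first aim is to "determine whether there is a benefit for patients regarding stress reduction when using video goggles". The second is to "determine whether any parameters can effectively measure such a potential benefit".

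**Primary end point (Assessment of Distress).** "The differences in serum cortisol levels between the groups are considered the primary end point". The same section lists the sampling times: "at baseline, arrival in the operation room, skin incision, clamping the carotid artery, skin suture, and 1 hour after skin suture". Of the first sample it says: "Baseline measurements are all taken under consistent conditions: the same time of day before the patient rises from bed". It does not say whether the primary difference refers to one of these times, a change from baseline, a peak, an average or an area under the curve.

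**Analysis (Planned Analysis).** "exploratory nature, descriptive statistics will be applied. Appropriate measures of central tendency and variability will be used depending on the level of measurement". Then: "Graphical representations will be made using line graphs or box plots". The Clinical Outcomes section announces comparisons between the arms at several times during surgery, but gives no method.

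**Purpose and size.** The Randomization section gives 100 patients allocated 1:1, without blinding. The Sample Size Estimation section says that no formal calculation was made and that the results are to be the basis for a confirmatory trial. The Discussion adds: "Although the sample size is limited, which may preclude statistically significant findings".

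**The concern.** A primary end point should be one quantity, fixed before the results are seen. Here the label covers up to six between-group differences. The first cannot show an effect, because that sample is taken before the patient leaves bed. The other five are all candidates, and nothing says which one carries the conclusion. In an unblinded trial with group profiles plotted over time, the eye goes to the widest gap. Calling the analysis descriptive does not prevent that.

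The stated analysis is also weaker than the first objective. Group-wise centres and spreads with plots show how each arm behaved. They do not state how large the difference between arms is, or how uncertain it is. A confirmatory trial would start from exactly that figure, for a named quantity.

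**Working it through.** The article derives no figure for this comparison (it gives no SD, effect size, alpha or power), so there is nothing to reproduce. The checks below size the consequences.

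**Inputs from the document:** 50 per arm; six cortisol samples, five of them after baseline.

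**Assumptions:** equal SD in both arms and at all times; approximately normal differences; a common between-time correlation of 0 to 0.7; a baseline correlation of 0.3 or 0.5.

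**1. Room for selection under no effect**

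- Standard error of a between-group difference, in SD units: sqrt(2/50) = 0.20.
- One time named in advance: P(|d| > 0.3) = P(|z| > 0.3/0.20) = P(|z| > 1.5) = 0.134.
- Any of five independent times: 1 − (1 − 0.134)^5 = 0.51.
- Any of five correlated times, by simulation (400,000 draws):

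| Between-time correlation | P(at least one of five differs by more than 0.3 SD) |
|---|---|
| 0 | 51% |
| 0.3 | 48% |
| 0.5 | 42% |
| 0.7 | 34% |

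The figure showing when the goggles are worn is not available here, so the number of samples that could reflect their use is unknown. If it were three, the probability would lie between 13% (correlation 1) and 1 − (1 − 0.134)^3 = 35% (correlation 0).

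**2. What a planned estimate would deliver**

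The 95% half-width in SD units is t × sqrt(2/n) × sqrt(1 − r²), where r is the correlation of the cortisol summary with baseline. For n = 50 per arm, t is about 1.984.

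| Baseline correlation r | Calculation | Half-width |
|---|---|---|
| unadjusted | 1.984 × 0.20 | 0.40 SD |
| 0.3 | 0.397 × sqrt(0.91) | 0.38 SD |
| 0.5 | 0.397 × sqrt(0.75) | 0.34 SD |

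The Data Collection and Management section excludes incomplete records. If 10% were lost (an assumption), 45 per arm would give an unadjusted half-width of 0.42 SD.

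These are half-widths for one summary, in units of that summary's own SD. On the log scale, the limits are exponentiated to give the geometric mean ratio.

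**The case against.** The best defence is that this is a declared pilot, called exploratory in several sections. Descriptive analysis is then a disclosed and legitimate choice. Where the summaries are means and SDs, a reader with the group sizes can work out an unadjusted difference and its interval, and the SDs help to plan the next trial. That stands, and it is why the point is not more serious. It does not settle which of the cortisol differences is primary. Nor does it make the wording of the first objective fit the analysis.

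Some stronger readings are tempting but not supported:

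- **That the analysis is unadjusted, or that baseline cortisol goes unused.** The article is silent. A full protocol or analysis plan may specify covariates.
- **That neither objective can be answered.** Group centres and spreads for cortisol, heart rate, RASS and KAB do inform the choice of parameters for a later trial.
- **That the second objective is circular**, because a parameter showing no group difference may be insensitive or the goggles may not work. Any trial of an unproven intervention has that limit. It is not an error in this plan.
- **That the plan has an inflated false-positive rate.** If each of the five post-baseline times had a 95% interval, the chance that at least one excluded zero would be about 15% to 21% (correlation 0.7 to 0.3). No intervals or tests are planned, so this is hypothetical.
- **That the Discussion promises significance tests.** Its remark on statistical significance is a stated limitation.

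**Conclusion.** The point holds, and it should be fixed. The primary cortisol comparison is left open across its sampling times, and the only stated analysis gives no between-group estimate with uncertainty. The first objective therefore claims more than the analysis can support, and the confirmatory trial gets no planned effect estimate.

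The room for selection is material: about 34% to 51% for a chance difference above 0.3 SD at one or more of five times, against 13% at a single pre-named time. The 0.3 SD threshold is illustrative, and the correlations are assumed. Fewer relevant samples would lower the figure. Baseline adjustment improves precision (0.40 to 0.34 SD at a correlation of 0.5). Validity does not depend on it, because allocation is randomised.

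**What to change.** Before the data are analysed:

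1. **Name one primary cortisol summary** over the intraoperative samples taken during goggle use, for example the mean log cortisol over those samples. Check the window against Figure 1 before fixing it.
2. **Report one contrast:** goggles minus control on that summary, adjusted for log baseline cortisol, presented as a geometric mean ratio with a 95% CI.
3. **Keep the other time points and parameters descriptive**, with no claim of significance.
4. **Reword the first objective** as estimating the effect of the goggles on stress.

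The cost is wording in the analysis plan and minor extra analysis work. The scheduled measurements already include everything needed. Recruitment was about 90% complete when the article was submitted and analysis is to follow the 100th patient, so the change must be recorded and dated before that analysis starts.
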